## 10.4 Description of Statistical Methods

### 10.4.1 General Approach

Results will be presented as means ± SD unless otherwise stated. Analysis of variance with a covariance (ANCOVA) test will be used in order to assess adherence to the interventions (attendance of the group sessions) and differences in changes nutrient intakes between the diet strategies. General linear models will be used to compare the trajectories of body weight and WC across the four intervention groups. We will use multivariate two-way ANCOVA and compare type of diet and physical activity as fixed factors (2*2 factorial design) to test changes in specific fat depots, using mean of differences and 95% CIs for each intervention group over time. Optional interactions between diet and exercise will be assessed by the ANCOVA models. To assess the effect of the combination of diet and PA, general linear models will be used with LFPA– as the reference. All models will be adjusted for age, sex, baseline abdominal obesity and 18-month weight change. Changes in the various fat depots and deposits will be evaluated both as absolute and relative changes. The association between changes in abdominal fat and intra-hepatic fat, and changes in levels of blood biomarkers will be tested using multivariate linear regression models, adjusted for age, sex, weight change, intervention group and baseline abdominal fat status (for the abdominal fat models) or baseline intra-hepatic fat (for the hepatic model). Homeostasis-model-assessment-of insulin-resistance (HOMA-IR) will be calculated according to the following equation: insulin (U/ml)×fasting glucose(mmol/liter) ÷22.5. Statistical analysis will be performed with IBM SPSS (version 23). All *P*-values will be two-sided, and *P*<0.05 will be considered statistically significant.

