# 3 OBJECTIVES AND PURPOSE

***Objective 1:***  To assess the effect of Low-carb/MED and Low- fat diets with or without PA on the dynamics of body fat compesition (mainly VAT) during weight loss and regain-plateau phases by 1.5-Tesla MRI.

***Objective 2:***  To assess the effect of Low-carb/MED and Low- fat diets with or without PA on the dynamics of abdominal suncotenius intra-hepatic fat among participants with abdominal obesity or dyslipidemia.

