### 4.2.1 Primary Endpoint

Changes in body fat compestion (mainly VAT) following the intervention

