# 6 STUDY AGENT

## 6.1 Study Agent(s) and Control Description

**Diet Intervention**

Both diets are aimed for a moderate, long-term, weight loss with restricted intake of *trans*-fats and refined carbohydrates, and increased intake of vegetables. Lunch, typically the main meal in this population, will be provided exclusively by the workplace cafeteria. A dietitian will be working closely with the kitchen staff to adjust the diets to the specific diet groups. The 18-month dietary intervention will include 90-minute nutritional session in the workplace with clinical dietitians every week during the first month of the intervention, and every month thereafter. Participants will be instructed to adhere to their specific diets during the entire week. To ensure that the intensity of treatment was equal between the two dietary intervention groups, the workshop format and the quality of the materials delivered during these sessions will be similar across the diet groups.

For the LF diet, the aim is to limit total fat intake to 30% of calories, with up to 10% of saturated fat, and no more than 300 mg of cholesterol per day, and to increase dietary fiber. Participants will be counseled to consume whole grains, vegetables, fruits, and legumes and to limit their consumption of additional fats, sweets, and high-fat snacks.

The MED/LC diet will combine the Mediterranean and low-carbohydrate diets described in our previous weight loss trial (the DIRECT trial^22^). The diet restricted carbohydrate intake to less than 40 g/day in the first two months (induction phase), and thereafter a gradual increase up to 70 g/day, and increased protein and fat intake, according to the MED diet. The MED/LC diet will be rich in vegetables and legumes and low in red meat, with poultry and fish replacing beef and lamb. This group will be also provided 28 g of walnuts/day [160 Kcal/84% fat, mostly PUFA (omega-3 α-linolenic acid)] starting from the third month, after the very low carbohydrate diet during the first two months.

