# 10 STATISTICAL CONSIDERATIONS

## 10.1 Statistical and Analytical Plans

The overall primary outcome is the change in body fat distribution, and the main specific endpoint is VAT, with a priori hypothesis that VAT, specifically, could be differentially and significantly altered by lifestyle intervention strategies. Secondary outcomes will be abdominal subcutaneous fat sub-depot and hepatic fat.

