## 10.3 Analysis Datasets

We will check the assumptions for all the statistical analyses to ensure that none were violated. We will perform intention-to-treat analyses, including all the participants, by imputing the missing observations for adipose tissues for the individuals with missing data at 18-months by the multiple imputation technique, with the following predictors: age, gender, baseline weight/ BMI and waist circumference at the end of the intervntion. For missing data of body weight, we will use the last observation carried forward.

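### The only specified model for the primary VAT endpoint adjusts for 18-month weight change, a result of the randomised treatment, so it does not estimate the effect of assigned diet and exercise

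*Protocol*

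**What the plan says.** Section 10.4.1 names the fat-depot model: "We will use multivariate two-way ANCOVA and compare type of diet and physical activity as fixed factors (2*2 factorial design) to test changes in specific" (the sentence goes on to name the depots). It adds a four-group general linear model with low-fat diet without added exercise as the reference. The covariate sentence follows directly: "All models will be adjusted for age, sex, baseline abdominal obesity and 18-month weight change". Section 10.4.2, on the primary endpoint, restates the outcome and gives no other model. No analysis without weight change is specified anywhere in the protocol.

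The question put to that model appears in four places:

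- Section 3, Objective 1: "To assess the effect of Low-carb/MED and Low- fat diets with or without PA on the dynamics of body fat compesition (mainly VAT").
- Section 4.2.1, primary endpoint: "Changes in body fat compestion (mainly VAT) following the intervention".
- Section 10.1, a priori hypothesis: "VAT, specifically, could be differentially and significantly altered by lifestyle intervention strategies".
- Section 10.3, analysis principle: "We will perform intention-to-treat analyses, including all the participants".

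None of the four conditions on weight. Section 6.1 says of the interventions: "Both diets are aimed for a moderate, long-term, weight loss".

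**The concern.** Weight change to month 18 is known only at the end of the trial, and both diets are designed to alter it. For months 6 to 18 the exercise assignment can alter it too. Holding it fixed has two consequences.

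1. Any part of the VAT effect that acts through weight loss is taken out of the arm coefficient.
2. If the arms differ in weight change, people with the same weight change in different arms are no longer comparable by design. Any unmeasured factor that drives both weight and VAT then confounds the comparison.

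At stake are the primary P-value and confidence interval. A strategy that lowers VAT mainly by lowering weight could be reported as having little or no effect on VAT, although the stated objective is to learn whether it has one.

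**Working it through.** **Inputs.** From section 10.5: minimum detectable difference δ = 3.57 cm², alpha 5%, power 80%, N = 250. From section 10.6.1: 1:1 allocation, 125 per diet. From section 10.4.1: two-sided tests. The protocol gives no SD of VAT change, no weight–VAT correlation and no expected arm difference in weight change. Those are assumptions below.

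**Step 1, the plan's own figure.** With n per arm = 2·SD²·(1.960 + 0.842)²/δ², the 250 cannot be reproduced without an SD. An SD of 9 gives 200 in total, 10 gives 248 and 12 gives 356. Solving for the SD that returns 125 per arm:

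SD = 3.57 / (2.802 × √(2/125)) = 3.57 / 0.3544 ≈ 10.07 cm²

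So δ is about 0.354 SD. This value presupposes the stated 80% power. It sets a scale and does not verify the sample size.

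**Step 2, what the adjusted model estimates.** Let r be the within-arm correlation of weight change with VAT change. Let d be the extra weight loss, in SD units, of the arm with the larger VAT loss. Without other common causes:

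- adjusted effect = 3.57 − r × 10.07 × d
- residual SD = 10.07 × √(1 − r²)

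For r = 0.5 the residual SD is 8.72 and the standard error is 8.72 × √(2/125) = 1.10.

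| d (SD) | Adjusted effect (cm²) | Power |
|---|---|---|
| 0 | 3.57 | 0.90 |
| 0.1 | 3.57 − 0.50 = 3.07 | 0.79 |
| 0.2 | 3.57 − 1.01 = 2.56 | 0.64 |
| 0.35 | 3.57 − 1.76 = 1.81 | 0.37 |

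Over r from 0.3 to 0.7 and d from 0.1 to 0.35, the effect shrinks by 8% to 69%. If the arm with the larger VAT loss loses less weight, d is negative: at d = −0.2 the adjusted effect is 3.57 + 1.01 = 4.58 cm², larger than the total effect.

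**Step 3, simulation check.** 4,000 runs, 125 per arm, total effect set at −3.57 cm², slope 0.6 SD of VAT change per SD of weight change:

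- No arm difference in weight change: unadjusted −3.57, power 0.80; adjusted −3.56, power 0.94.
- Half of the effect through weight (arm difference 0.30 SD): unadjusted −3.54, power 0.80; adjusted −1.75, power 0.39.
- All of the effect through weight (arm difference 0.59 SD): unadjusted −3.58, power 0.79; adjusted −0.02, rejection rate 0.05.

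**Step 4, a shared unmeasured cause.** Give one unmeasured factor loadings of 0.4 on both weight and VAT change, with slope 0.5, no direct effect and a total effect of −3.57 cm². The arm difference in weight change is then 0.354/0.5 = 0.71 SD. The within-arm regression of VAT on weight is 0.5 + 0.4 × 0.4 = 0.66 rather than 0.5. The adjusted coefficient is therefore (0.66 − 0.5) × 0.71 × 10.07 = +1.14 cm², which has the wrong sign. The simulation also gave +1.14, rejecting 19% of the time. This is an unfavourable case: the error is proportional to the arm difference in weight change, so at 0.2 SD it would be 0.16 × 0.2 × 10.07 = 0.32 cm².

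**The case against.** The strongest reply is that a weight-independent effect may be what the trial wants. Section 2.1 calls for trials of whether the diet adds VAT loss over and above that from losing weight. Section 2.2 frames the thesis as a more favourable effect on abdominal depots at comparable overall weight loss. Section 10.1 defines the overall primary outcome as a change in fat distribution. If the diets do produce equal weight change, adjustment leaves the diet estimate unchanged and improves its precision, as Step 3 shows.

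The interest is genuine and justifies keeping the weight-adjusted model, but not as the only one. No objective, endpoint or hypothesis is worded conditionally on weight. Equal weight loss cannot be presumed: section 2.1 reports similar weight dynamics across the earlier trial's arms but also better weight loss on low-carbohydrate. Section 4.1 and Table 2 restrict energy in one arm only, while section 10.6.1 calls the diets equal in calories. Section 2.2 speaks of the diets, not of a year of supervised exercise. Plain covariate adjustment also isolates a direct effect only if nothing unmeasured drives both weight and VAT change, and the protocol does not argue this.

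A reader might infer more than the documents support:

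- That adjustment must shrink the estimate. It may leave it unchanged or inflate it, depending on the arm difference in weight change.
- That the covariate lies wholly after both randomisations. Months 0 to 6 precede the exercise randomisation.
- That the weight analysis is adjusted for its own result. "General linear models will be used to compare the trajectories of body weight and WC across the four intervention groups" falls under the covariate sentence if read literally, but that sentence sits among the fat-depot models, so loose wording is at least as likely. A clarification is enough.
- That carrying the last weight forward (section 10.3) materially corrupts the covariate. No missing-data rate is given, so this cannot be sized.

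**Conclusion.** The point stands and should be settled before analysis. As written, the sole primary VAT model estimates a weight-conditional contrast, while the objective, endpoint, hypothesis and intention-to-treat statement call for the effect of assignment. That mismatch follows from the text alone.

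Its numerical size does not. On the back-solved SD of 10.07 cm², with r from 0.3 to 0.7 and arm differences of 0.1 to 0.35 SD in the favourable direction, the estimated effect falls by 8% to 69%. It is unchanged if the arms lose equal weight and inflated if the difference runs the other way. With a shared unmeasured cause and an effect that acts wholly through weight, it can change sign. The protocol does not show which of these applies to the diet or the exercise contrast.

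**What to change.** In section 10.4.1, remove 18-month weight change from the primary and secondary fat-depot models. Specify diet, physical activity, their interaction and pre-randomisation covariates only: age, sex, baseline VAT (or the baseline value of the depot analysed) and the randomisation strata in section 10.6.1. Weight change to month 6 is no substitute, because it follows the diet randomisation.

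Keep the weight-adjusted model as a labelled supportive analysis of the effect beyond weight loss, stating that it is not a comparison protected by randomisation. Add one sentence that the body-weight and waist-circumference models are not adjusted for weight change.

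The cost is a wording change and one extra labelled model. Some reduction in residual variance is lost, which baseline VAT should partly replace.

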# PROTOCOL SUMMARY

| **Title:** | **Differential effect of weight-loss diet strategies on dynamics of abdominal and other fat depots and metabolic risk – the CENTRAL study: intervention trial** |
| --- | --- |
| **Précis:** | **Methods**: an estimate of 250 participants who have either a. central obesity or b. lean participants with poor dietary habits combined with hyper TG will be randomized by median VAT to the following groups: **Group 1:** low-fat diet. **Group 2 :** Low-carb /Mediterranean high MUFA and PUFA diet diet. Specific food items will be provided. After 6 months of intervention, the diet groups 1 and 2 will be re-randomized to continue with diet only or with combination of 4 hours/week aerobic and resistance gym exercise for the subsequent year, divided by 4 equal size groups of **Group A** (low-fat diet only), **Group A+** (low-fat diet +physical activity) , **Group B** (Low-carb/ high MUFA & PUFA diet only) and **Group B+** (Low-carb/ high MUFA & PUFA diet + physical activity). All groups will be guided for their dietary intervention by nutritional sessions. All the participants will be followed by 1.5-Tesla MRI imaging of fat and muscle, blood and urine biomarkers, clinical measurements (weight, waist circumference, blood pressure, energy expenditure) and electronic questionnaire of dietary, lifestyle and medical information. Furthermore, genetic tests will be performed following a genetic ethical committee approval. |
| **Objectives:** | To assess whether distinct lifestyle strategies can differentially affect specific body adipose pools.  ***Objective 1:***  To compare the effects of: low-carb/high-MUFA; and the currently recommended diet by the American Heart Association (low-fat diet) on the dynamics of body fat compesition (mainly VAT) during weight loss and regain-plateau phases by MRI with and without physical activity. ***Objective 2:***  To assess the effect of Low-carb/MED and Low- fat diets with or without PA on the dynamics of abdominal suncotenius intra-hepatic fat among participants with abdominal obesity or dyslipidemia. |
| **Endpoint** | Primary Endpoint: Body fat composition (changes in VAT). Important Secondary Endpoints: changes in abdominal subcutaneous fat sub-depots and hepatic fat. |
| **Population:** | Healthy adults with abdominal obesity/dyslipidemia. |
| **Phase:** | Phase 3 |
| **Number of Sites enrolling participants:** | Nuclear Research Center-Negev, Dimona, Israel  250 participants |

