## 6.2 Study agent Accountability Procedures

# 7 STUDY PROCEDURES AND SCHEDULE

## 7.1 Study Procedures/Evaluations

### 7.1.1 Study specific procedures

**Magnetic Resonance Imaging (MRI)**

To assess body fat depots/deposits, we will perform a 45-minute 1.5-Tesla MRI (Ingenia 3.0 T, Philips Healthcare, Best, the Netherlands) scans at baseline and after 18 months. In a sub-set of, randomly selected, 50% of the participants, we will perform MRI measurement after 6 months of intervention. The scanner utilize a 3D modified DIXON (mDIXON) imaging technique without gaps (2mm thickness and 2mm of spacing), fast-low-angle shot (FLASH) sequence with a multi-echo two-excitation pulse sequence for phase-sensitive encoding of fat and water signals (TR,3.6ms; TE1,1.19ms; TE2,2.3ms; FOV 520×440×80mm; 2×1.4×1mm voxel size). Four images of the phantoms will be generated, including in-phase, out-phase, fat and water phase. A breath-hold technique will be used to avoid motion artifacts when the chest and abdomen will be scanned. In all simultaneous fat depots quantifications and comparisons, observers will be blinded to time point and group treatment. All fat depots will be assessed by one or two raters. To validate our mDIXON quantification of fat ratio, we will test five tubes filled with 0%, 25%, 50%, 75% and 100% of oil to observe a linear relation.

***Abdominal fat depots:*** We will quantify abdominal fat using the MATLAB-based semi-automatic software. We will calculate mean VAT and SAT from three axial slices: L5-S1, L4-L5 and L2-L3. Quantification of the fat mass regions will include the area of each fat type and its proportion (percentage) of the total area of all fat types.

***Hepatic fat content:*** We will quantify the percentage of hepatic fat using PRIDE software from Philips Medical Systems. We will calculate mean percentage from four 2D slices (3cm intervals divided into quarters) by utilizing the region of interest (ROI) approach, which is based on measurements of tissue densities (fat/fat+water) using the Fat Ratio Calculation.

***Resting metabolic Rate (RMR)*** We will mesure RMR by indirect calorimetry (QUARK REE by COSMED, Rome, Italy) in which the quantity of oxygen consumed and carbon dioxide produced are measured and converted into kcal using the Weir equation.

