### 10.4.2 Analysis of the Primary Efficacy Endpoint(s)

The overall primary outcome is the change in body fat distribution, and the main specific endpoint is VAT.

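### VAT change is tested on two scales and over several contrasts at an unadjusted 0.05, and no scale or contrast is named as deciding the primary result

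*Protocol*

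**What the plan says.** **Endpoint.** Section 4.2.1 gives the primary endpoint as "Changes in body fat compestion (mainly VAT) following the intervention". The Protocol Summary has "Primary Endpoint: Body fat composition (changes in VAT", section 10.4.2 reads "The overall primary outcome is the change in body fat distribution, and the main specific endpoint is VAT", and section 10.1 adds an "a priori hypothesis that VAT, specifically, could be differentially and significantly altered by lifestyle intervention strategies". Sections 4.2.2 and 10.4.3 make abdominal subcutaneous and hepatic fat secondary.

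**Scale.** Section 10.4.1: "Changes in the various fat depots and deposits will be evaluated both as absolute and relative changes". Neither scale is given precedence.

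**Contrasts.** The same section fits a 2×2 model with diet and PA as factors and allows an optional interaction. For the combination of diet and PA, "general linear models will be used with LFPA" (no added PA) as the reference group, which gives three further comparisons.

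**Decision rule.** All P-values are two-sided, and P below "0.05 will be considered statistically significant". Section 10.5 takes alpha 5%, power 80%, a detectable VAT difference of 3.57 cm² between the intervention groups, and 250 participants. It does not say which groups.

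**The concern.** Section 10.4.2 is headed as the primary efficacy analysis, yet it restates the endpoint and names no scale, contrast or test. The only operative rule is the general one in 10.4.1, which treats each VAT result alike at 0.05. Absolute and relative change need not agree, because relative change weights participants by their baseline VAT. The contrasts also answer different questions.

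The hypotheses do not settle the matter. Section 10.2 speaks of two opposing diets, whereas section 10.1 speaks of lifestyle strategies in general. At stake is what a positive result means: with several equal-ranking tests and no stated order, the 5% in section 10.5 is not the error rate for a claim about VAT.

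**Working it through.** **The plan's own figure.** Section 10.5 gives no standard deviation, so N = 250 cannot be reproduced, only back-solved:

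SD = 3.57 × √(n/2) / (1.960 + 0.842), with n per group.

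- Diet against diet, n = 125: 3.57 × 7.906 / 2.802 = 10.07 cm².
- Two of the four final groups, n = 62.5: 3.57 × 5.590 / 2.802 = 7.12 cm².

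Neither SD is in the protocol, so the arithmetic cannot show which contrast was sized. The point below does not depend on it.

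**Counting the tests of VAT in section 10.4.1.** Diet, PA, interaction and three groups against the reference make 6 contrasts. On two scales that is 12 tests.

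**Chance of at least one P < 0.05 when nothing works.** For k independent tests it is 1 − 0.95^k. The six contrasts are all built from the same four group means, and the two scales are correlated, so that formula overstates the rate for the larger sets. A simulation was therefore run: 40,000 trials for each assumed correlation, 250 participants in four groups of 62-63, a 2×2 linear model with pooled-error t-tests, and no covariates or missing data. Correlations between absolute and relative change of 0.70, 0.80, 0.90 and 0.95 were assumed.

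| VAT tests | Scales | k | 1 − 0.95^k | Simulated |
|---|---|---|---|---|
| Diet | 1 | 1 | 5.0% | 4.9-5.2% |
| Diet, PA | 1 | 2 | 9.75% | 9.7-9.9% |
| Diet, PA, interaction | 1 | 3 | 14.3% | 14.1-14.6% |
| All six contrasts | 1 | 6 | 26.5% | 18.7-19.1% |
| Diet | 2 | 2 | 9.75% | 6.5-8.2% |
| All six contrasts | 2 | 12 | 46.0% | 23.2-29.3% |

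The one-scale rows need no assumption about correlation; their ranges are simulation noise. In the two-scale rows the low end belongs to correlation 0.95 and the high end to 0.70. As a check on that range, relative change was drawn with mean −20% and SD 20%, and baseline VAT with a coefficient of variation of 0.3 to 0.5 (all assumed). The correlation between the scales was then 0.92 to 0.82, inside the range used.

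**Power cost of two confirmatory contrasts.** Holm's first step tests at 0.025 two-sided. The detectable difference grows by (2.2414 + 0.8416) / (1.9600 + 0.8416) = 3.0830 / 2.8016 = 1.10. If 3.57 cm² refers to a main effect, it becomes 3.57 × 1.10 = 3.93 cm².

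**The case against.** **Six contrasts is the broad reading.** The interaction is optional, the reference-group comparisons re-express the same four means, and section 10.2 points to diet as the lead question. Diet alone carries 5% on one scale and 6.5-8.2% on two. Many statisticians also regard the two main effects of a factorial trial as separate questions, each entitled to 5%. This stands as a reason to quote a range and not to insist on shared alpha. It does not cover the interaction, the three reference comparisons or the second scale.

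**The scale is partly signalled.** Section 10.5 states the detectable effect in cm². But it reaches that figure from a relative change of 12.8%, and 10.4.1 then ranks both scales equally.

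**The SAP may settle it.** Alpha allocation is often left to an SAP, which is not at hand, and the empty heading at 10.4.9 is not counted against the plan. The point rests on what 10.4.1 does state. An SAP that named one deciding test would still sit beside a protocol rule that calls every P < 0.05 significant.

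**Stronger readings that the text does not support.**

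- From section 4.2.1 alone a reader might infer that the fat depot is left open. The Protocol Summary and sections 10.1, 10.4.2 and 10.4.3 fix VAT as the main endpoint and make the other depots secondary.
- A reader might double the count to 24, because the MRI section says that quantification "will include the area of each fat type and its proportion (percentage) of the total area of all fat types". That sentence describes what the software measures. Nothing says that VAT's share of fat will be compared between groups.
- A reader might conclude that any significant VAT test will be reported as the primary result. The protocol leaves that possible but does not say it.

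**Conclusion.** The point holds as a matter of specification. VAT is fixed as the endpoint; the deciding scale and contrast are not, and the stated rule does not hold the error rate for a VAT claim at 5%. Depending on how many of the tests in 10.4.1 are counted, the rate is about 10% (two main effects, one scale), about 19% (six contrasts, one scale) or about 23-29% (six contrasts, two scales). That is roughly two to six times the nominal level.

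The first two figures follow from the contrasts alone. The last depends on an assumed correlation of 0.95 to 0.70. The independence values of 26.5% and 46.0% should not be quoted as the actual rates. No conclusion is drawn about whether 250 participants is adequate.

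**What to change.** Amend sections 4.2.1, 10.4.1 and 10.4.2 to state:

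- **Primary variable:** absolute change from baseline to 18 months in mean VAT area over the three slices, in cm², the unit used in section 10.5.
- **Confirmatory contrast(s):** either the diet main effect alone at two-sided 0.05, or the diet and PA main effects by Holm at an overall 0.05.
- **Everything else on VAT:** relative change, the interaction and the comparisons with low-fat without added PA are secondary, with no confirmatory claim. The P < 0.05 sentence should be limited to match.

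The cost is wording only: no new data or participants. With one contrast there is no loss of power, and the simulated error rate is the nominal 5%. With two under Holm, the detectable difference rises by at most 10%, from 3.57 to 3.93 cm² if 3.57 refers to a main effect, which section 10.5 should also state. Keeping all the tests as confirmatory would be dearer: Bonferroni would need 0.05/6 = 0.0083 on one scale or 0.05/12 = 0.0042 on two.
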